### Inclusion Criteria

To be included in the study, the participants had to be aged between 5 and <20 years at the initial examination for the natural progression study and between 8 and <16 years at the initial examination for the intervention study. Furthermore, the parents must have read, understood, and signed the informed consent form, and the participants must have read, understood, and signed the assent form. The participants in the intervention groups had to agree to wear the prescribed contact lenses for a minimum of 10 hours per day, at least 6 days per week, for the 2-year duration of the intervention period and be in good general health with no contraindications to contact lens wear. Additionally, the following criteria had to be met: maximum manifest spherical refractive error of +6.00 D, maximum manifest cylindrical refractive error of −1.00 D, minimum anisometropia of >1.00 D in the anisohyperopic group (mean spherical error), maximum anisometropia of 1.00 D in the nonanisohyperopic group (mean spherical error), and minimum mean spherical refractive error of +2.00 D in the more hyperopic eye. Furthermore, participants had to be competent at handling contact lenses and understand the instructions provided to ensure safe wear.

### Exclusion Criteria

The exclusion criteria were as follows: previous contact lens wear, participation in another clinical study, regular use of medication to treat ocular conditions, current use of systemic medication that may have an impact upon successful contact lens wear or vision, known ocular or systemic disease, findings identified during contact lens assessment that would preclude contact lens wear, and not being able to provide informed consent without the aid of an interpreter, as no funding was available for the provision of interpreter facilities.

### Ethical Approval

The study was granted ethical approval by the National Health Service Research Ethics Committee on May 26, 2016, and by Aston University Research Ethics Committee on June 2, 2016. The trial is registered at ClinicalTrials.gov (NCT02686879).

### Sample Size

Sample size has been calculated using G*Power (version 3.1.9; Franz Faul, Universität Kiel, Germany) for a significance level of alpha=.05 at 80% power while also allowing for attrition.

### Statistical Analyses

All data will be analyzed using the commercially available software SPSS version 23 (IBM, NY, United States) using a repeated-measures mixed analysis of variance design with 1 between-subject factor and 1 within-subject factor. Principal outcomes measures are: change in axial eye growth and change in refractive error.

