For the study, healthy hyperopic children and adolescents will be recruited via the researchers’ optometry practices and Aston University's Eye Clinic. A database search will be performed by the immediate research team to identify potential participants who meet the criteria for inclusion; these individuals will be contacted via post with information regarding the study and how to participate. A poster will also be displayed at both research venues as a means of recruiting other potential participants. Contact details will be stated on the poster to enable anyone interested in joining the study to contact the researcher for further details.

All participants, including parent(s) or guardian(s), expressing an interest in joining the study or wishing to recruit their child into the study will be provided detailed information regarding the study and will have the opportunity to ask questions before completing the consent form declaration.

Allocation to the contact lens-wearing and the natural progression arms of the study will not be randomized. Individuals who are willing and able to use contact lenses will be given the opportunity to be included in the contact lens arm of the study; those who do not want to wear, are unable to handle, or unsuitable for contact lenses will be given the opportunity to participate in the natural progression arm of the study.

After obtaining informed consent, all participants will undergo a number of visual assessments including a background questionnaire, axial length measures, subjective refraction, accommodative lag, amplitude of accommodation, stereopsis, vision and visual acuity, postcycloplegic objective refraction, postcycloplegic peripheral refraction at 30**°** temporally and nasally, and 20**°** superiorly and inferiorly, and pupil size.

For the natural progression study, the normal growth of the eyes will be followed at 7 visits over 3 years without any intervention. A topical cycloplegic (cyclopentolate hydrochloride 1%) will be used on visits 1, 2, 4, 6, and 7 (Table 1).

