Participants in the intervention arms of the study will also have the normal growth and visual characteristics of the eyes followed at 7 visits over 3 years. In addition, they will have their suitability for contact lens wear determined at the second visit, 6 months after the first visit, which will require instructions on contact lens wear and follow-up appointments. In total, for participants in the intervention arms of the study, there will be 9 scheduled visits, with a cycloplegic used on visits 1, 2, 6, 8, and 9 (Table 2). There may be unscheduled visits if any problems arise as a result of contact lens wear. The participants, with parental support where necessary, will be instructed on how to insert, remove, and care for their contact lenses.

**Table 1 table1:** Procedures for participants in the natural progression arm of the study.

Procedure	Visit 1 (month 1)	Visit 2 (month 6)	Visit 3 (month 12)	Visit 4 (month 18)	Visit 5 (month 24)	Visit 6 (month 30)	Visit 7 (month 36)
Informed consent	✓	✓	✓	✓	✓	✓	✓
Questionnaire	✓	✓	✓	✓	✓	✓	✓
Axial length	✓	✓	✓	✓	✓	✓	✓
Subjective refraction	✓	✓	✓	✓	✓	✓	✓
Accommodative lag	✓	✓	✓	✓	✓	✓	✓
Amplitude of accommodation	✓	✓	✓	✓	✓	✓	✓
Stereopsis	✓	✓	✓	✓	✓	✓	✓
Vision and visual acuity	✓	✓	✓	✓	✓	✓	✓
Postcycloplegic refraction	✓	✓		✓		✓	✓
Peripheral refraction	✓	✓		✓		✓	✓

**Table 2 table2:** Procedures for participants in the intervention arms of the study.

Procedure	Visit 1 (month 1)	Visit 2 (month 6)	Visit 3 (month 7)	Visit 4 (month 8)	Visit 5 (month 12)	Visit 6 (month 18)	Visit 7 (month 24)	Visit 8 (month 30)	Visit 9 (month 36)
Informed consent	✓	✓			✓	✓	✓	✓	✓
Questionnaire	✓	✓			✓	✓	✓	✓	✓
Axial length	✓	✓			✓	✓	✓	✓	✓
Subjective refraction	✓	✓			✓	✓	✓	✓	✓
Accommodative lag	✓	✓			✓	✓	✓	✓	✓
Amplitude of accommodation	✓	✓			✓	✓	✓	✓	✓
Stereopsis	✓	✓			✓	✓	✓	✓	✓
Vision and visual acuity	✓	✓			✓	✓	✓	✓	✓
Postcycloplegic refraction	✓	✓				✓		✓	✓
Peripheral refraction	✓	✓				✓		✓	✓
Pupil size					✓				
Contact lens fitting		✓							
Contact lens aftercare			✓	✓	✓	✓	✓	✓	

For the anisohyperopes, the more hyperopic eye will be fitted with a commercially available soft multifocal contact lens and the less hyperopic eye will be fitted with a soft single-vision contact lens, if required. Participants with similar levels of hyperopia in each eye will be fitted with commercially available soft multifocal contact lenses in both eyes.

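### The planned repeated-measures ANOVA, as usually run in SPSS, uses only children with a value at every level of the within-subject factor, so a 3-year study that expects attrition would discard observed data

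*Protocol article*

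**What the plan says.** The Statistical Analyses section of the protocol article fixes both software and method: "All data will be analyzed using the commercially available software SPSS version 23", "using a repeated-measures mixed analysis of variance design with 1 between-subject factor and 1 within-subject factor". The outcomes follow: "Principal outcomes measures are: change in axial eye growth and change in refractive error". The section does not name the SPSS procedure. It also does not say whether the within-subject factor is visit or eye, or how many levels it has.

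Under Study Design, for the natural progression arm, "the normal growth of the eyes will be followed at 7 visits over 3 years without any intervention". Participants in the intervention arms "will also have the normal growth and visual characteristics of the eyes followed at 7 visits over 3 years"; their two extra visits, at months 7 and 8, are for lens aftercare only (Table 2). The cycloplegic "will be used on visits 1, 2, 4, 6, and 7" in the natural progression arm, and the intervention schedule is "with a cycloplegic used on visits 1, 2, 6, 8, and 9". By Tables 1 and 2 these are the same five months in all arms: 1, 6, 18, 30 and 36.

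Under Sample Size, the calculation was done "for a significance level of alpha=.05 at 80% power while also allowing for attrition". No rate, effect size, standard deviation or number of participants is given. Study Design also states that allocation is not randomised and depends on willingness and ability to wear lenses.

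**The concern.** The design named is the classical split-plot ANOVA. Its standard SPSS form needs a complete set of repeated measures for each subject. A child without a value at one level of the within-subject factor is left out of the whole analysis, including the visits that were attended.

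Two things are at stake:

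- **Precision.** Over 3 years in children and adolescents, permanent dropout and occasional missed visits both reduce the number analysed. An attrition allowance sized for permanent dropout does not cover the second source.
- **Bias.** Complete-case analysis is safe only if completers represent everyone enrolled. The arms are formed by choice and carry different burdens, because lens wearers commit to 2 years of near-daily wear. Reasons for leaving could therefore differ between arms. If leaving also depends on growth seen so far, the difference among completers is distorted. A likelihood-based model that uses the earlier visits can correct for that; the complete-case ANOVA cannot.

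This concerns a method the article does choose. A later analysis plan would have to replace the choice, not just add detail to it.

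**Working it through.** The article states no figure that could be reproduced, so the checks below use assumed rates.

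**Inputs from the article:** 80% power and alpha 0.05 (Sample Size); 7 axial-length visits, hence 6 follow-ups after the first; 5 cycloplegic visits, hence 4 follow-ups (Study Design, Tables 1 and 2).

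**Assumptions:** two-sided test; first visit always attended; each follow-up visit missed independently with probability m; enrolment already inflated for permanent dropout, so that these misses come on top of it; visit is the within-subject factor, with all visits as levels.

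**Step 1, share complete:** f = (1 − m)^k, with k = 6 or 4.

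**Step 2, power:** Φ((1.96 + 0.84)·√f − 1.96). At f = 1 this returns 80%.

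| m | f, 7 visits | power | f, 5 visits | power |
|---|---|---|---|---|
| 3% | 0.97^6 = 0.833 | 72% | 0.97^4 = 0.885 | 75% |
| 5% | 0.95^6 = 0.735 | 67% | 0.95^4 = 0.815 | 72% |
| 10% | 0.90^6 = 0.531 | 53% | 0.90^4 = 0.656 | 62% |

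**Step 3, enrolment for 100 complete cases:** at an assumed 20% permanent dropout, 100 / 0.80 = 125. If 5% of visits are also missed, 100 / (0.80 × 0.735) = 170.1, so 171.

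**Step 4, the mildest time factor:** if the factor has only a start and an end level, the share kept at 20% dropout is 0.80 × (1 − m). That is 78%, 76% or 72% for m of 2%, 5% or 10%. Intermediate misses then remove nobody, but a child without the end visit is still lost and the intermediate measurements go unused.

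**Step 5, bias:** a simulation with 400 runs, 150 children per group, seven half-yearly visits and permanent dropout only. All inputs are assumed: growth of 0.10 against 0.15 mm per year (a true 3-year difference of 0.15 mm), between-child slope SD 0.075 mm per year, and measurement SD 0.03 mm. The likelihood analysis was given the true covariance, which favours it slightly.

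| Dropout | Completers | Complete-case estimate (SD) | Likelihood, all visits (SD) |
|---|---|---|---|
| Unrelated to growth | 77% | 0.151 (0.0285) | 0.151 (0.0259) |
| Lens arm: slower observed growth, more dropout | 76% | 0.185 (0.0296) | 0.149 (0.0272) |

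In the first row complete-case analysis loses only precision. In the second it overstates the difference by about 23% (0.185 / 0.15 = 1.23).

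**The case against.** The strongest reply is that the article does not fix the configuration that causes the loss. SPSS 23 also offers MIXED, which keeps incomplete cases, and the procedure is not named. The factor could be eye, since the anisohyperopic element compares paired eyes, or start against end; in either case a missed intermediate visit drops nobody. This stands as a limit on the claim: a reader might infer that every child with any missed visit is certain to be dropped, and the text does not say so. It does not remove the point. The design named is an ANOVA, its ordinary implementation deletes incomplete cases, and Step 4 shows that a start-to-end factor still loses children and leaves data unused.

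The second reply is that the sample size already allows for attrition. That is true, and the size of the allowance is not given. The power figures above therefore apply only to misses beyond it and are not this study's power. An allowance can restore power but cannot remove bias. Independence is also the pessimistic case: if misses cluster in the same children, more of them stay complete.

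Several stronger readings are tempting but unsupported:

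- **Completers as adherent wearers.** Deletion follows attendance, not lens wear. Study Design says the intervention may stop on reaching a refractive threshold, but not that follow-up then ends.
- **The cycloplegic schedule as missing data.** Months 12 and 24 are omitted by design in all arms, and the two outcomes can be analysed with different levels.
- **Sphericity.** Nothing in the article shows a violation, and SPSS provides corrections.

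**Conclusion.** The point holds in a conditional form and is worth acting on before analysis. As usually run, the ANOVA the article chooses discards observed data in a 3-year study that expects attrition. It can also bias the comparison of non-randomised arms if missingness is related to earlier growth and differs between them. The article makes such bias plausible but does not demonstrate it.

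On assumed rates of 3% to 10% of follow-up visits missed independently, over and above any dropout allowed for, roughly one child in six to nearly one in two would be lost from a 7-visit analysis. Power would be about 72% down to 53%. The 5-visit analysis loses less. The 23% distortion in the simulation illustrates one assumed dropout mechanism and is not a forecast for this trial.

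**What to change.** Replace the repeated-measures ANOVA with a likelihood-based linear mixed model, available in the same software as MIXED, and state:

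- all available visits are used, with visit as a categorical factor;
- a covariance structure suited to the sample size (an unstructured matrix for seven visits has 7 × 8 / 2 = 28 parameters, which may be too many);
- eye enters as a within-child factor in the paired-eye arm;
- all children with follow-up data are kept, whether or not they continued lens wear.

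The cost is a slightly more complex model and a few sentences in the analysis plan. No new data or software are needed.

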**Methods:**

There are 3 elements to the program of research. First, the natural progression of axial eye growth and refractive error will be measured in spectacle-wearing hyperopic and anisohyperopic subjects aged between 5 and <20 years. In other words, the natural growth of the eye will be followed without any intervention. Second, as a paired-eye control study, anisohyperopes aged between 8 and <16 years will be fitted with a center-near multifocal design contact lens in their more hyperopic eye and a single-vision contact lens in the fellow eye if required. The progression of axial eye growth and refractive error will be measured and compared. Third, subjects aged between 8 and <16 years with similar levels of hyperopia in each eye will be fitted with center-near multifocal design contact lenses in each eye; the progression of axial eye growth and refractive error in these subjects will be measured and compared with those of subjects in the natural progression study.

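### The one stated model has a single within-subject factor, but the paired-eye anisohyperopic study has two (eye and visit) and no between-subject treatment factor

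*Protocol article*

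**What the plan says.** The Statistical Analyses section opens with "All data will be analyzed using the commercially available software SPSS version 23" and continues in the same sentence with the model: "using a repeated-measures mixed analysis of variance design with 1 between-subject factor and 1 within-subject factor". The factors are not named, and no other model is given for any part of the programme. The next sentence sets the outcomes: "Principal outcomes measures are: change in axial eye growth and change in refractive error".

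The design of the anisohyperopic element is described elsewhere in the same article:

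- Abstract, Methods: "as a paired-eye control study, anisohyperopes aged between 8 and <16 years will be fitted with a center-near multifocal design contact lens" in the more hyperopic eye, with a single-vision lens in the fellow eye where one is needed.
- Study Design: for anisohyperopes, "the more hyperopic eye will be fitted with a commercially available soft multifocal contact lens".
- Study Design, on the intervention arms: participants "will also have the normal growth and visual characteristics of the eyes followed at 7 visits over 3 years". Table 2 shows axial length at all seven of these visits and postcycloplegic refraction at five.

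For the hyperopic element, Study Design says: "Participants with similar levels of hyperopia in each eye will be fitted with commercially available soft multifocal contact lenses in both eyes". The Abstract says these participants are compared with those in the natural progression study, which also enrols anisohyperopes.

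**The concern.** In the paired-eye study the treatment contrast is between two eyes of one child, and each eye is measured repeatedly. Two factors therefore vary within the child, while the stated model offers one within-subject place. The remaining place is for a between-subject factor, and the paired-eye comparison has none.

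This is not a detail that a condensed article leaves to a fuller document. The article fixes the number and type of factors and applies them to everything, including an element that it calls paired-eye.

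At stake is the reason for using the fellow eye as control. Growth in the two eyes of a child is expected to be positively correlated, and a paired analysis removes that shared variation from the error term. An analyst who follows the sentence literally, with visit within and eye between, treats the two eyes as if they came from different children. A real effect of the lens on eye growth could then be reported as absent.

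**Working it through.** **Inputs.** Alpha .05 and 80% power come from the Sample Size section; a two-sided test is assumed, since sidedness is not stated. The article gives no sample size, effect size, standard deviation or inter-eye correlation, so there is no figure of its own to reproduce. The inter-eye correlation of change, r, is an assumption, shown at 0.6, 0.8 and 0.9.

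**Step 1: count the factors.**

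| Comparison | Between-subject | Within-subject | Fits 1 + 1? |
|---|---|---|---|
| Treated hyperopes vs natural progression, one value per child | arm | visit | yes |
| Anisohyperopes, treated vs fellow eye | none | eye and visit | no |

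**Step 2: visit within, eye between.** With n children and SD s of change in each eye, the variance of the mean eye difference is 2s²(1 − r)/n when paired and is taken as 2s²/n when pairing is ignored. The standard error used is therefore too large by 1/√(1 − r):

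- r = 0.6: 1/√0.4 = 1.58
- r = 0.8: 1/√0.2 = 2.24
- r = 0.9: 1/√0.1 = 3.16

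**Step 3: power.** A paired design sized for 80% has a true standardised effect of 1.96 + 0.84 = 2.80. Using the inflated standard error is the same as raising the critical value from 1.96 to 1.96/√(1 − r), so power = Φ(2.80 − 1.96/√(1 − r)):

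- r = 0.6: Φ(2.80 − 3.10) = Φ(−0.30), about 38%
- r = 0.8: Φ(2.80 − 4.38) = Φ(−1.58), about 6%
- r = 0.9: Φ(2.80 − 6.20) = Φ(−3.40), under 0.1%

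A shortcut that only divides 2.80 by the standard-error ratio and keeps unit variance for the statistic would give 43%, 24% and 14%. It is wrong, because the spread of the statistic shrinks by the same ratio.

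**Step 4: direction of the error.** The true type I error under this coding is 2[1 − Φ(1.96/√(1 − r))]: about 0.002 at r = 0.6 and below 0.0001 at 0.8 and 0.9. The test is conservative.

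**Step 5: simulation check.** This used 20 children, two eyes, seven visits, linear growth with eye slopes correlated at 0.7 (slope SD 1, measurement SD 0.3) and a slope difference of 0.6 under the alternative.

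| Analysis | Rejection under null | Power |
|---|---|---|
| Eye between, visit within | 0.002 | 0.38 |
| Eye and visit both within | 0.044 | 0.79 |
| Eye within, one change score per eye | 0.046 | 0.74 |

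Measurement noise lowers the correlation of the estimated slopes to 0.7/(1 + 0.09/0.778) = 0.63, so the 0.38 is in line with the formula near r = 0.6. Across correlations from 0 to 0.9, null rejection with eye and visit both within was 0.044 to 0.052.

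**Step 6: eye within, one change score.** Pairing is kept, as the third row shows. But a change between two visits leaves 7 − 2 = 5 axial-length visits unused, in a study built around a 6-month run-in, 2 years of lens wear and 6 months after withdrawal.

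**The case against.** The strongest reply is that the sentence names neither factor and that the principal outcomes are changes. Time can then sit inside the outcome, which leaves the within-subject slot for eye. The natural progression arm includes anisohyperopes, so arm can fill the between-subject slot. Two layouts therefore fit one plus one and keep the pairing: arm by eye on a change score, or arm by visit on the interocular difference.

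This stands as far as it goes. A reader might infer from the sentence that pairing must be lost and the error term must be wrong. The article does not support that, because the loss follows only if eye is placed between subjects. But the article states neither of the two valid layouts. Both bring in untreated anisohyperopes as a second, non-randomised comparison, whereas the Abstract describes the fellow eye as the control. The first also sets the intermediate visits aside.

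A reader might also infer that the hyperopic arm, with both eyes treated, will have its eyes entered as independent cases and its type I error inflated. Nothing in the article says so. With one value per child, arm by visit is a correct analysis there, and the choice between one eye and the mean of two is a detail that an article may leave to the full protocol.

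**Conclusion.** The point holds in a limited form. The stated factor structure does not match the paired-eye study: one within-subject slot cannot carry both eye and visit, and the paired-eye comparison has no between-subject treatment factor. The text as written admits both valid and invalid analyses.

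The size depends on how the slots are filled. Under the worst coding (visit within, eye between), power falls from 80% to about 38%, 6% or under 0.1% for r of 0.6, 0.8 or 0.9. Under the change-score coding, the cost is the unused intermediate visits: power 0.74 against 0.79 in the simulated case. These figures rest on the assumed correlations, a two-sided test and, for the first set, a design sized on the paired comparison; the article does not say which comparison was powered.

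It would go too far to conclude that the stated alpha and power hold in neither intervention study. That would need an unstated coding in one arm and an unstated double count in the other. With positive inter-eye correlation, the risk shown here is a missed effect, not a false positive.

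**What to change.** Do not delete the model; limit it and add to it.

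- **Treated hyperopes versus natural progression:** keep one between-subject factor (arm) and one within-subject factor (visit), name both, and analyse one value per child.
- **Anisohyperopic study:** replace the stated layout with eye and visit both within-subject, the eye by visit interaction as the test of interest and the child as the independent unit. Alternatively, analyse the within-child interocular difference (treated minus fellow eye) in change.
- If untreated anisohyperopes are also to serve as a comparison group, state this as a separate analysis of the interocular difference, with arm between subjects and visit within.

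The cost is a few lines of analysis wording and a different SPSS specification. No new data or visits are needed. The change should be made before the data are analysed.
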